### Exploratory Outcomes

#### fMRI Usage

fMRI is an important tool for studying psychoneural mechanisms by detecting blood oxygen level–dependent signals in brain activity and is also an important means for evaluating therapeutic effects [31]. The fMRI will be used to identify the brain regions associated with the PNSCs in ovarian cancer and to assess the changes following treatment. fMRI is planned for 30 randomly selected patients per group, totaling 60 participants. Assessments will be conducted at baseline and 3 months after enrollment.

#### Biological Targets in Peripheral Blood

Differential protein expression will be measured using targeted proteomics in patients with cancer and PNSCs before and after treatment, with the goal of exploring potential actionable therapeutic targets. The study will randomly select 50 cases from each group, totaling 100 patients for examination. Assessments will be conducted at baseline and at 3 months after enrollment.

#### Biological Targets in Tumor Tissue

Some proteins are involved in both the biological processes of tumors and the generation of psychoneurological symptoms [32]. Targeted proteomics will be performed exclusively on tumor tissues obtained before treatment to detect differentially expressed proteins between patients with cancer and PNSCs and cancer-free controls. Additionally, common biological targets in peripheral blood and tumor tissue samples will be explored. The study will randomly select 50 cases from each group, totaling 100 patients for examination. Tumor tissue will be collected at baseline.

#### Tumor Markers

CA125 and HE4—which are routinely used in combination for monitoring ovarian cancer—will serve as the primary monitoring indicators [33]. Additional data on related markers (including CA19-9 and CEA) will be concurrently collected to enable a comprehensive analysis. Assessments will be conducted at baseline and 3 months after enrollment.

#### Proportions of Immune Cells

The proportions of immune cells, such as T cells, B cells, and natural killer cells, will be measured. The study will randomly select 50 cases from each group, totaling 100 patients for examination. Assessments will be conducted at baseline and at 3 months after enrollment.

#### Cytokine Levels

The expression levels of cytokines, such as interleukin-6, interleukin-10, tumor necrosis factor-α, and interferon-γ, will be measured. The study will randomly select 50 cases from each group, totaling 100 patients for examination. Assessments will be conducted at baseline and at 3 months after enrollment.

#### Functional Assessment of the Hypothalamic-Pituitary-Adrenal Axis

Hypothalamic-pituitary-adrenal (HPA) axis function will be assessed by measuring plasma adrenocorticotropic hormone, urine free cortisol, and plasma cortisol levels. Adrenocorticotropic hormone is a pivotal mediator within the axis, while cortisol serves as its primary effector hormone; elevated cortisol levels typically indicate a physiological stress state [34]. Fifty cases will be randomly selected from each group, totaling 100 patients for testing. Assessments will be conducted at baseline and at 3 months after enrollment.

#### Analysis of Immune Gene Expression

RNA sequencing analysis will be performed on patient-derived biological samples to investigate expression changes in immune-related genes, with a specific focus on their roles in immune regulation. This study will randomly select 50 cases from each group, totaling 100 patients for research. Assessments will be conducted at baseline and at 3 months after enrollment.

### Safety Outcomes

Vital signs (respiration, body temperature, heart rate, and blood pressure) will be monitored at baseline and at 1, 2, 3, 6, 9, and 12 months after enrollment. Laboratory test indicators—including complete blood count (white blood cells, hemoglobin, and platelets), urinalysis (urine protein and urine white blood cells), liver and kidney function (alanine aminotransferase, aspartate aminotransferase, and serum creatinine), and electrocardiogram (ECG [electrocardiography] findings and QT interval)—will be assessed at baseline and at 3 months. All findings will be categorized based on clinical significance as normal, abnormal but not clinically significant, or abnormal and clinically significant.

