#### Dropout Criteria

The dropout criteria are as follows:

Occurrence of complications, comorbidities, or serious adverse events (SAEs) making continued participation in the trial inadvisable.Investigator determination that discontinuation or suspension of the clinical trial is warranted for safety reasons.Withdrawal from the study by the subject for any reason.Participants retain the right to withdraw from the trial at any time. Investigators should document the reason for withdrawal to the extent possible.

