### Follow-Up

During the 3-month treatment period, follow-up visits will be scheduled once per month. After the completion of treatment, follow-up assessments will be performed every 3 months. The total follow-up duration will be 1 year. Data collection time points are presented in Table 2.

**Table 2. T2:** Study timeline.

Study stage	Screening and baseline period	Treatment period			Follow-up period		
Visit (times)	0	1	2	3	4	5	6
Time point (day)	−14 to 0	30	60	90	180	270	360
Time window (day)	+3 or −3	+3 or −3	+3 or −3	+3 or −3	+7 or −7	+7 or −7	+7 or −7
Collection of basic medical history							
Informed consent	✓						
Emission standards	✓						
Demographic data	✓						
Diagnosis and treatment history	✓						
Assessments of validity							
MDASI-OC^a^ scale	✓	✓	✓	✓	✓	✓	✓
PSQI^b^ sleep scale	✓	✓	✓	✓	✓	✓	✓
PFS-R^c^ scale	✓	✓	✓	✓	✓	✓	✓
PHQ-9^d^ depression scale	✓	✓	✓	✓	✓	✓	✓
GAD-7^e^ anxiety scale	✓	✓	✓	✓	✓	✓	✓
EORTC QOL-C30^f^ scale	✓	✓	✓	✓	✓	✓	✓
TCM^g^ syndrome scale	✓	✓	✓	✓	✓	✓	✓
One-year OS^h^ rate and PFS^i^ rate							✓
Sleep quality	✓	✓	✓	✓			
Sleep diary	✓	✓	✓	✓			
fMRI^j^	✓			✓			
Biological targets in peripheral blood	✓			✓			
Biological targets in tumor tissue	✓						
Tumor markers	✓			✓			
Proportions of immune cells	✓			✓			
Cytokine levels	✓			✓			
HPA^k^ axis function	✓			✓			
Analysis of immune gene expression	✓			✓			
Vital signs	✓	✓	✓	✓	✓	✓	✓
Laboratory Test Indicators and ECG^l^	✓			✓			
AE^m^ and SAE^n^	✓	✓	✓	✓	✓	✓	✓

a MDASI-OC: MD Anderson Symptom Inventory for Ovarian Cancer.

b PSQI: Pittsburgh Sleep Quality Index.

c PFS-R: Piper Fatigue Scale-Revised.

d PHQ-9: Patient Health Questionnaire-9.

e GAD-7: Generalized Anxiety Disorder-7.

f EORTC QOL-C30: European Organisation for Research and Treatment of Cancer Quality of Life Questionnaire - Core.

g TCM: traditional Chinese medicine.

h OS: overall survival.

i PFS: progression-free survival.

j fMRI: functional magnetic resonance imaging.

k HPA: hypothalamic-pituitary-adrenal.

l ECG: electrocardiography.

m AE: adverse event.

n SAE: serious adverse event.

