### Adverse Events

Adverse events (AEs) are defined as any undesirable or negative experience or outcome that does not have a causal relationship with the treatment. Although the treatment regimens used in clinical research have undergone initial safety evaluations, individual differences may lead to unexpected adverse reactions in some participants. All AEs will be recorded, and appropriate management will be immediately provided. Furthermore, participants are guaranteed by state health insurance and are permitted to withdraw from the study at any stage without any consequences.

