### Data Collection and Management

#### Data Entry and Modification

Data collection, entry, and modification will be conducted using the EDC and electronic Patient-Reported Outcome systems. The study will provide all participants with protocol-required laboratory and imaging tests at no cost, along with a fixed travel allowance for follow-up visits, to enhance patient adherence to follow-up visits. Participants who discontinue the study intervention or deviate from the protocol will be withdrawn from the study. Only the data from the last follow-up visit prior to withdrawal will be recorded. Two data managers will be responsible for data entry and verification. For questions in the EDC, the data manager will revise and confirm the data according to the original data of patients and the answers of researchers to ensure the overall data quality. Upon completion of data entry, consistency checks will be performed, and the database will be locked.

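### A participant who stops granules before the day-90 visit window opens has no scheduled post-baseline laboratory or ECG/QT value, even if stopped for safety

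*Protocol article*

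**What the plan says.** Three parts of the Protocol article bear on this.

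- **Schedule.** Safety Outcomes lists blood count, urinalysis, ALT, AST, creatinine and ECG with QT interval, and says they "will be assessed at baseline and at 3 months". Results are then graded: "All findings will be categorized based on clinical significance as normal, abnormal but not clinically significant, or abnormal and clinically significant". In Table 2 (Follow-Up), the row "Laboratory Test Indicators and ECG" is ticked at visit 0 and visit 3 (day 90) only. Vital signs and adverse events are ticked at every visit.
- **Stopping.** Data Entry and Modification states: "Participants who discontinue the study intervention or deviate from the protocol will be withdrawn from the study". It continues: "Only the data from the last follow-up visit prior to withdrawal will be recorded".
- **Reasons for stopping.** Dropout Criteria includes "Occurrence of complications, comorbidities, or serious adverse events (SAEs) making continued participation in the trial inadvisable", and also a decision by the investigator on safety grounds. It adds: "Investigators should document the reason for withdrawal to the extent possible".

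On adverse events, the section of that name says "All AEs will be recorded, and appropriate management will be immediately provided". Data Monitoring requires each event to be followed until it has resolved or settled.

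**The concern.** Each rule is clear alone; the difficulty comes from combining them. The only post-baseline laboratory and ECG time point is day 90, and a participant who stops earlier leaves the study before reaching it. Participants taken off granules for a safety reason belong to that group, and theirs are results a reader of the safety section would particularly want to see.

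Safety is part of the primary objective (Objectives). If the rules are followed as written, the comparison of laboratory and QT findings between full-dose and 10%-dose granules describes those who stayed to visit 3. The analysis cannot restore the missing values: under Missing Value Handling, multiple imputation covers efficacy end points only, and safety relies on observed events.

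**Working it through.** **Step 1: what a participant has, by time of stopping (Table 2 and Data Entry and Modification).**

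| Granules stopped | Last recorded visit | Scheduled post-baseline laboratory/ECG sets |
|---|---|---|
| Before visit 1 (day 30) | 0 | 0 |
| Between visits 1 and 2 | 1 | 0 |
| After visit 2 (day 60), before the visit 3 window | 2 | 0 |
| Within the window before day 90, visit 3 already done | 3 | 1 |
| After visit 3 | 3 | 1 |

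The window for visit 3 is 3 days either side of day 90, so it opens on day 90 − 3 = 87. Someone who stops on days 87 to 89 may already have been tested.

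**Step 2: frequency of assessment.** Laboratory tests and ECG are ticked at 2 of 7 visits (0 and 3), and at 0 of the 2 visits between baseline and day 90. Adverse events and vital signs are ticked at 7 of 7.

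**Step 3: the plan's own dropout figure (Sample Size).** The inputs are remission of 40% and 10%, margin 15%, one-sided alpha 0.025 and power 0.80. With unpooled variance, n = [0.40 × 0.60 + 0.10 × 0.90] × (1.960 + 0.842)² / (0.30 − 0.15)² = 115.1, so 116 per group. Allowing for 20% dropout, 116 / 0.80 = 145 per group. Both figures match the protocol, which then raises the size to 158 per group, 316 in total.

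**Step 4: illustrative scale.** The protocol does not say when dropout occurs or how it divides between arms. The table assumes an equal split. The 20% row assumes that all planned dropout falls before day 90; the 10% and 5% rows are assumptions.

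| Share stopping before day 90 | Total without a value | Per group without | Per group with |
|---|---|---|---|
| 20% | 316 × 0.20 = 63.2 | 158 × 0.20 = 31.6 | 158 × 0.80 = 126.4 |
| 10% | 316 × 0.10 = 31.6 | 158 × 0.10 = 15.8 | 158 × 0.90 = 142.2 |
| 5% | 316 × 0.05 = 15.8 | 158 × 0.05 = 7.9 | 158 × 0.95 = 150.1 |

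**The case against.** **Adverse events are followed after stopping.** Data Monitoring requires follow-up to resolution or stability and sets no end at withdrawal. It also provides for reporting of serious events and cumulative review by the principal investigator. This stands, and it defeats one tempting inference, that a participant stopped for safety receives no further attention. A recognised event may well lead to unscheduled tests. But the section names no laboratory test or ECG, and it acts only on events somebody has noticed. A rise in ALT or creatinine, or a change in QT, without symptoms would not be noticed without a test.

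**The recording rule may not cover safety data.** Read as barring every later record, it would conflict with the Adverse Events and Data Monitoring sections. The reading that reconciles them is that it governs scheduled visit data while adverse event data continue. That is fair. The gap in scheduled tests remains on that reading, and the text should say which reading is meant.

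**A condensed article may leave out an early-termination visit.** The full protocol may contain one. The article is not merely silent, however: it states withdrawal on discontinuation and limits what is kept, which points the other way.

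**The consequence is modest.** Laboratory and ECG results are summarized descriptively, no decision rule is described for them, and reasons for withdrawal are documented where possible. This stands and limits the weight of the point.

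**Conclusion.** The point holds for scheduled tests. Under the rules as written, a participant who stops granules before the visit 3 window opens has no scheduled post-baseline laboratory or ECG/QT value, whatever the reason for stopping. The laboratory and QT summary would then rest on participants who reach visit 3.

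Two further inferences are not supported:

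- **That the summary would be biased in favour of the granules.** Nothing in the document shows that the missing values would differ from the observed ones, or differ by arm, so no size or direction is claimed.
- **That 63 of 316 is a maximum.** The 20% is a planning allowance for all dropout, including people who leave for reasons unrelated to safety, and actual dropout could be higher or lower. The figures of about 63, 32 and 16 are illustrations that rest on the assumed timing.

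This is a low-cost improvement to consider. It is not a flaw in the efficacy analysis.

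**What to change.** 1. In Safety Outcomes, and as a footnote to the laboratory/ECG row of Table 2, state that the second set of tests is done *at 3 months, or at the time of stopping granules if earlier*.
2. In Data Entry and Modification, state that these results, and any results from adverse event follow-up, are recorded after discontinuation and included in the safety summary.
3. Report the number in each arm with no post-baseline laboratory or ECG value.

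The cost is a few sentences, one footnote and one entry in the data capture system. The tests are already planned and are brought forward, so no participant has an extra scheduled set. The protocol reports no recruitment as of April 2026; if that is still so, the change can apply from the first participant.

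The downsides are values taken at uneven times, slightly more data entry, and some stoppers who will decline or not attend, as they are free to do. For that reason the fix may recover fewer values than the illustrative totals suggest. It also adds no laboratory or ECG check during dosing for those who continue.

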### Adverse Events

Adverse events (AEs) are defined as any undesirable or negative experience or outcome that does not have a causal relationship with the treatment. Although the treatment regimens used in clinical research have undergone initial safety evaluations, individual differences may lead to unexpected adverse reactions in some participants. All AEs will be recorded, and appropriate management will be immediately provided. Furthermore, participants are guaranteed by state health insurance and are permitted to withdraw from the study at any stage without any consequences.

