### Objectives

The primary objective of this study is to evaluate the efficacy and safety of the TSZA regimen in alleviating PNSCs among patients with ovarian cancer. The secondary objectives include assessing its impact on patients’ quality of life and survival outcomes. Furthermore, the study aims to explore the characteristics of the patient population that derives benefit from the TSZA regimen for these symptoms.

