#### Missing Value Handling

Missing data will be handled according to the type and role of each variable. For missing diagnosis dates, original pathology records will be retrieved whenever possible. If the pathology report date is unavailable, the date of surgery will be used for imputation. If neither source can be obtained, the date of the patient’s first visit for ovarian cancer will be used, with the month imputed as July of that year and the day as the first day of the month. For baseline demographic and clinical characteristics, no imputation will be performed, and available data will be summarized descriptively. For safety outcomes, only observed AEs will be included in the analysis without imputation. For primary and secondary efficacy end points, missing follow-up data will be handled using multiple imputation under the missing at random assumption. The imputation model will include treatment group, baseline outcome values, and key prognostic covariates. Complete case analysis will be performed as a sensitivity analysis to assess the robustness of the primary findings.

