#### Data Monitoring

The data monitoring committee for this experiment will be made up of 4 experts who are not involved in the research team. The committee will be in charge of external oversight, monitoring the study’s viability, data integrity, and safety. A risk-based monitoring approach will be adopted, primarily through random audits. Data with poor compliance or containing modifications in the EDC system will be subject to targeted review.

AEs must be documented in detail, appropriately managed, and tracked until resolution or stabilization. SAEs and unanticipated problems shall be reported in a timely manner to the Ethics Committee, the competent regulatory authority, the sponsor, and other relevant oversight bodies as required.

Study progress reports shall be submitted on schedule, including explanations for any AEs, subject withdrawals, and protocol deviations. The principal investigator will periodically conduct cumulative reviews of all AEs and, when necessary, convene investigator meetings to evaluate the risk-benefit profile of the study.

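### The only adverse event definition shown requires that the event was not caused by treatment, so non-serious treatment-related events have no stated recording route

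*Protocol article*

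**What the plan says.** The definition is in the Adverse Events section: "Adverse events (AEs) are defined as any undesirable or negative experience or outcome that does not have a causal relationship with the treatment". The sentence after it warns that "individual differences may lead to unexpected adverse reactions in some participants", and the section then commits to the following: "All AEs will be recorded, and appropriate management will be immediately provided".

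Other sections use the same term without redefining it:

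- Missing Value Handling: "For safety outcomes, only observed AEs will be included in the analysis without imputation".
- Data Monitoring: "AEs must be documented in detail, appropriately managed, and tracked until resolution or stabilization". The same section puts AEs into the progress reports and has the principal investigator review all AEs cumulatively.
- The study timeline (Table 2, under Follow-Up) schedules AE and SAE collection at every visit.

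The Objectives section makes safety part of the primary objective, which is to "evaluate the efficacy and safety of the TSZA regimen in alleviating PNSCs among patients with ovarian cancer". Participants Research Protection provides compensation for harm that is medically judged to be related to the study.

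**The concern.** Whether an event is related to treatment is normally a judgement attached to an event already recorded. Here the absence of a causal link is a condition of being an AE at all, so the judgement comes before recording and acts as a filter. An investigator who suspects that the granules caused a symptom would, by following the sentence, leave it out of the AE record.

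The events at risk are those the safety part of the primary objective most needs: non-serious clinical events attributable to the study treatment. An event never recorded cannot be recovered at analysis, and the multiple imputation planned for efficacy does not apply to safety.

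**Working it through.** The document gives no AE rate, so there is no stated figure to reproduce. The check is mainly a comparison of sections.

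**Step 1. Is the definition corrected elsewhere?** Dropout Criteria, Follow-Up, Safety Outcomes, Missing Value Handling, Data Monitoring, Final Analysis and Participants Research Protection were read for a second definition. None gives one, and none defines a separate category, such as adverse drug reaction, that would catch the excluded events.

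**Step 2. Does it fit the rest of the protocol?** No. The next sentence expects adverse reactions, which are treatment-caused by meaning. The compensation clause presupposes that related harm is identified. The safety objective concerns harm from the regimen. All three conflict with a definition that excludes related events.

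**Step 3. What depends on the term?**

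| Activity | Section | Limited to AEs? |
|---|---|---|
| Recording | Adverse Events | Yes |
| Event analysis | Missing Value Handling | Yes |
| Documentation and tracking | Data Monitoring | Yes |
| Cumulative review by the principal investigator | Data Monitoring | Yes |
| Vital signs (every visit); laboratory tests and ECG (baseline and 3 months) | Safety Outcomes | No causality condition |
| Reporting of SAEs and unanticipated problems | Data Monitoring | No causality condition stated |

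A non-serious symptomatic event judged related falls under the first four rows and is excluded from them. The last two rows catch it only if it also shows in a scheduled measurement or counts as an unanticipated problem.

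**Step 4. Direction and possible size (assumed rates).** Suppose 20% of participants in each arm have a background event and a further 10% at full dose have a drug-caused event. The true rates are then 30% and 20%. For simplicity, each participant has at most one event and the low-dose control causes none. Let p0 be the share of background events judged related and p1 the share of drug-caused events judged related. Dropping those events gives:

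- recorded rate, full dose = 20(1 − p0) + 10(1 − p1)
- recorded rate, control = 20(1 − p0)
- recorded difference = 10(1 − p1)

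| p0 | p1 | Full dose | Control | Difference | Ratio |
|---|---|---|---|---|---|
| 0 | 0 | 30% | 20% | 10 points | 30/20 = 1.50 |
| 0.3 | 0.3 | 14 + 7 = 21% | 14% | 7 points | 21/14 = 1.50 |
| 0.1 | 0.5 | 18 + 5 = 23% | 18% | 5 points | 23/18 = 1.28 |
| 0 | 1 | 20 + 0 = 20% | 20% | 0 points | 1.00 |

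The absolute difference shrinks whenever any drug-caused event is filtered out. The ratio shrinks only if drug-caused events are judged related more often than background events. The last row needs perfect causal attribution in both directions.

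**The case against.** The best case on the other side has four parts.

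- **It is a slip.** A word such as necessarily has probably been lost. The protocol expects adverse reactions, collects AEs at every visit, allows emergency unblinding for SAEs and compensates related harm. None of this suggests an intention to discard related events, and many sites would record them anyway. This stands as an account of how the sentence arose. It does not make the sentence right: it is the only definition shown, and investigators are to be trained on the research plan.

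- **Much safety information is unaffected.** A reader might infer that treatment-related harm disappears from the safety data altogether. The document does not support that. Vital signs, laboratory tests and ECG are collected and classified by clinical significance whatever the cause, and Data Monitoring says "SAEs and unanticipated problems shall be reported in a timely manner to the Ethics Committee" with no causality condition stated. The loss is confined to AE data, chiefly non-serious clinical events. The backstop is nevertheless partial, because laboratory tests and ECG are done only at baseline and 3 months.

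- **Oversight is not shown to be blind.** A reader might also infer that the data monitoring committee sees only AEs as defined, or that its cumulative review would miss related events. The cumulative AE review belongs to the principal investigator, and the committee's safety task is stated without being limited to AEs.

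- **Blinding limits the bias.** Investigators cannot filter by arm, and safety is only summarised descriptively, with no between-arm AE test stated. It is therefore too strong to say that the comparison is blind to harm or that a difference would be erased. Blinding does not remove the tendency, though: if the full dose causes more events than the 10% control, a filter on relatedness has more to remove in that arm.

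**Conclusion.** Wrong as written. The sentence inverts the role of causality, contradicts its own section and the safety objective, and governs recording, analysis, documentation and the principal investigator's review. Applied literally, it would under-record non-serious events judged treatment-related and would tend to narrow any excess at full dose.

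The size is unknown. It depends on how often investigators judge events related and on how many sites follow the sentence literally, and the document gives neither. The illustrated narrowing from 10 points to 7, 5 or 0 rests entirely on assumed rates, and the zero is a worst case. If every site ignores the wording and records all events, nothing is lost. The conclusion that the text needs correcting does not depend on these assumptions.

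**What to change.** Redefine an AE as any untoward medical occurrence after enrollment, whether or not it is considered related to treatment. State that relatedness is assessed as an attribute of a recorded event and is not a condition for recording it. Then align the Adverse Events, Missing Value Handling and Data Monitoring sections with that definition.

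The details of a relatedness field and of AE tables by arm may already be in the full protocol, case report form or SAP. Their absence from an article is not criticised here.

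The cost is essentially one sentence, a consistency check and submission of the amendment to the lead ethics committee. No patients, visits or assessments are added. The Results section reports no recruitment as of April 2026, so a correction made before recruitment starts affects no collected data.
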